| Endpoints
(Primary/Secondary) | 
Primary endpoints:
 
1a Level of neutralizing antibodies against wild-type and immune escape variants in the 3 study groups at 10, 30, 90 and 180 days post boost.
 
1b Level of neutralizing antibodies against wild-type and immune escape variants at 10, 30, 90 and 180 days post 3rd immunization.
 
Secondary endpoints:
 
 
1. Level of T cell responses against SARS-CoV-2 spike protein peptides pools per subgroup at 30 days.
 
2. Occurrence of breakthrough infection with wild type, B.1.351 and other immune escape variants of SARS-CoV-2
 
3. Occurrence of adverse events, serious adverse events and adverse events of special interest
 
4. The clinical course (hospitalization, ICU admission) and outcome of COVID-19 diseases (recovery, long-Covid mortality).
 
5. Occurrence of adverse events, serious adverse events and adverse events of special interest after 3rd immunization
 
6. Level of T cell responses against SARS-CoV-2 spike protein peptides pools in non-responders after 3rd immunization
 
7. Occurrence of breakthrough infection with wild type, B.1.351 and other immune escape variants of SARS-CoV-2 after 3rd immunization
 
 |

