### **Lack of efficacy (vaccine failure)**

Lack of efficacy (vaccine failure) is defined as 2 consecutive positive tests for SARS-CoV-2 within a week (2 PCRs OR one antigen test + one PCR), independent of potential symptoms. These cases will be reported and documented as Serious Adverse Reactions (“lack of efficacy”). A higher frequency in the combination regimen (Arm A) as would be expected based on the efficacy profile of Comirnaty® or Vaxzevria® will be reported to the BASG as SUSAR.

In case of infection in vaccinated individuals, the cases will be reported to the authorities, incl. mutation analysis, advised to stay at home and if symptomatic treated according to the guide lines (Covid-19 guide lines). If these vaccine failures occur significantly more frequently in the heterologous than in the homologous arm, which is extremely unlikely based on previous experience with heterologous vaccination regimes containing adenovirus vectors, the study will immediately be terminated. An amendment to the study plan will be submitted. If predictors for vaccine failures in the heterologous arm can be determined (low neutralizing antibody levels), individuals with this predictor will receive a 2nd Comirnaty vaccination and followed up.

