## **7.3 Serious Adverse Events**

If a serious adverse event (SAE) occurs, the investigator must alert the sponsor without unjustified delay to any AE (whether causally or not) from this study that results in one of the following outcomes, or is significant for any other reason:

- death (excluding death from progressive disease)
- a life-threatening experience – refers to an event in which the subject was at risk of death at the time of the event; it does not refer to an event which hypothetically might have caused death if it were more severe
- initial hospitalization, or prolongation of existing inpatients’ hospitalization
- persistent or significant disability or incapacity
- congenital anomaly or birth defect

Additionally all Thrombosis with Thrombocytopenia Syndrome (TTS)/Vaccine-induced Thrombotic Thrombocytopenia (VITT) will be classified as serious adverse event.

Medical judgment should be exercised in deciding whether an AE/adverse drug reaction (ADR) is serious in other situations. Important AE/ADRs that are not immediately life-threatening or do not result in death or hospitalization but may jeopardize the subject or

may require intervention to prevent one of the other outcomes listed in the definition above, should also be considered serious.

Patients should be closely observed for adverse events while receiving treatment with the IMP. Further on for 12 weeks after discontinuation from study therapy in order to detect delayed toxicity. After this period, the clinical trial medical safety desk will only be alerted to serious adverse events if the investigator believes that the event may have been caused by the investigational device or by a protocol procedure.

Events not considered to be serious adverse events are hospitalizations for the:

- routine treatment or monitoring of the studied indication, not associated with any deterioration in condition
- treatment, which was elective or pre-planned, for a pre-existing condition that did not worsen
- treatment on emergency, outpatient basis for an event not fulfilling any of the definitions of serious given above and not resulting in hospital admission.

Disease progression will not be reported as AE or SAE unless the progression is unexpected in severity or early occurrence. Progressive disease will be appropriately documented on the case report form as part of the efficacy parameters.

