## 7.4 Adverse Drug Reaction (ADR) & Unexpected Adverse Drug Reaction

Noxious and unintended responses to a IMP related to any dose should be considered adverse drug reactions. The phrase responses to a medicinal product means that a causal relationship between a medicinal product and an adverse event is at least a reasonable possibility, i.e. the relationship cannot be ruled out.

Regarding marketed medicinal products: a response to a drug which is noxious and unintended and which occurs at doses normally used in man for prophylaxis, diagnosis, or therapy of diseases or for modification of physiological function (see the ICH Guideline for Clinical Safety Data Management: Definitions and Standards for Expedited Reporting).

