## 11. Statistics

### 11.1 Sample Size

The sample size is generated for the primary endpoint of a superiority testing of level of neutralizing antibodies against the B.1.351 variant between the two randomized study arms (arm 1: ChAdOx1-S prime & boost, arm 2: ChAdOx1-S prime and BNT162b2 boost). A comparison against arm 3 (BNT162b2 prime & boost) is exploratory and will be done descriptively.

In a study of Madhi  92% of participants showed neutralizing antibodies following vaccination with ChAdOx1-S prime & boost against the B.1.1.7 (British) variant and 58% against the B.1.351 (South African) variant. Focusing on the improvement of the heterologous vaccination with the Biontech boost against the South African variant with regard to primary the endpoint of neutralizing antibodies we consider a sample size of n=1000 per study arm as appropriate. With this sample size, we can detect an increase in the percentage of participants with neutralizing antibodies against the South African variant from 58% to 65.5% as statistically significant, with a power of >90% and alpha of 5%. If the increase is 10% the statistical power would be >99%.

For the secondary endpoint of efficacy against breakthrough infection with the B.1.351 variant, based on the current number of 8 new cases per week in Tyrol with the B.1.351 variant we expect 208 cases during the next 180 days with no change in rate of infection.

Currently, the B.1.351 is concentrated in 4 districts – Kufstein, Schwaz, Innsbruck Land and Innsbruck Stadt giving a total population of 416,758, this gives a rate of 49,9/100,000 people in 180 days. As not all cases are sequenced we estimate that only 5% of B.1.351 variants are detected, this would mean in total a rate of approximately 1000 cases per 100000 population of the B.1.351 variant would occur over 180 days – this means 10 cases per 1000. This scenario could lead to 10 cases in the ChAdOx1-S prime & boost arm (Arm 1) and 0 case in the ChAdOx1-S prime and BNT162b2 boost arm (Arm 2). In the extreme situation that all 10 cases occur in Arm 1, this would be statistically significant. However, due to the decreasing infection rates in Tyrol we would currently consider this an underpowered analysis and as such would perform a posthoc power analysis. In addition, a second immune escape variant, B.1.1.7.+E484K has recently occurred in Tyrol with over 900 cases until now. However, the development of this outbreak is currently not predictable.

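### Vaccine failures are coded as Serious Adverse Reactions whatever the symptoms, and nothing keeps them out of the SAE totals, so those totals mix infections with vaccine harms

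*Protocol*

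**What the plan says.** Protocol section 7.2 has a paragraph on lack of efficacy. Its definition reads "Lack of efficacy (vaccine failure) is defined as 2 consecutive positive tests for SARS-CoV-2 within a week", met by two PCRs or by one antigen test plus one PCR, and it applies "independent of potential symptoms". The coding instruction is "These cases will be reported and documented as Serious Adverse Reactions", with the label lack of efficacy in brackets.

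The general rules sit elsewhere. Section 7.3 lists outcomes that make an event serious, such as "initial hospitalization, or prolongation of existing" inpatient stay, and leaves other cases to medical judgment. Section 7.4 says "Noxious and unintended responses to a IMP related to any dose should be considered adverse drug reactions". Section 7.8 has the investigator assess causality for each event.

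In the Synopsis, secondary endpoint 2 is "Occurrence of breakthrough infection with wild type, B.1.351 and other immune escape variants of SARS-CoV-2" and secondary endpoint 3 is "Occurrence of adverse events, serious adverse events and adverse events of special interest". Endpoints 7 and 5 repeat these after the third dose. The safety analysis in 11.3.5 is a descriptive tabulation of adverse events by treatment group. It does not mention lack-of-efficacy cases.

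**The concern.** A participant with no symptoms and two positive tests meets none of the outcomes listed in 7.3, and a positive test is hard to describe as a noxious response to the vaccine. Section 7.2 nevertheless makes the case both serious and related, without the individual judgment that 7.3, 7.4 and 7.8 call for. Section 7.3 also routes disease progression to the efficacy parameters rather than to AE or SAE reporting, which points the other way.

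Weekly testing from Day 7 to Day 182 (5.7, 5.10.2) means symptom-free infections will be found. Each qualifying case is then counted once for efficacy and once as a related serious event. Section 7.9.2 adds to this: after the first week it asks for deaths, SAEs and other events of concern believed to be related, and a case pre-coded as related passes that filter automatically. Section 7.3 gives a different, 12-week period, so the sizes below do not rely on this point.

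At stake is the reading of the overall SAE and related-SAE incidence. Safety of the heterologous regimen is a named secondary objective, and those two totals would depend on how much virus was circulating as well as on harm from the vaccine.

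**Working it through.** **1. Reproduce the planning rate (11.1).** Inputs: 8 cases per week, 208 cases in 180 days, population 416,758, 5% of cases detected.

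- 8 × 26 weeks = 208 cases
- 208 / 416,758 = 49.9 per 100,000
- 49.9 / 0.05 = 998 per 100,000 = 9.98 per 1000

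This agrees with the protocol's "this means 10 cases per 1000".

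**2. Share of counted SAEs that would be infections.** Let *i* be infections per 1000 and *s* all other SAEs per 1000 in the same arm. The share is *i* / (*i* + *s*). Take *i* = 10. The protocol gives no value for *s*, so it is an assumption, equal in both arms.

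| *s* per 1000 (assumed) | Counted SAEs per 1000 | Share that are infections |
|---|---|---|
| 2 | 12 | 10/12 = 83% |
| 5 | 15 | 10/15 = 67% |
| 10 | 20 | 10/20 = 50% |
| 20 | 30 | 10/30 = 33% |
| 30 | 40 | 10/40 = 25% |

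With 10 infections per 1000 in both arms, the SAE rate ratio between arms stays at 1.0. The effect is then inflation in each arm, with no difference between them.

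**3. What unequal infection rates would do.** Section 11.1 describes an extreme scenario of 10 cases in the homologous Vaxzevria arm and 0 in the heterologous arm, 1000 per arm. For the infections alone, Fisher's exact p = 0.0019, so the protocol's statement that this would be significant reproduces. Adding the same assumed *s* to both arms gives:

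| *s* per 1000 (assumed) | SAE counts | Rate ratio | Fisher p |
|---|---|---|---|
| 2 | 12 vs 2 | 6.0 | 0.013 |
| 5 | 15 vs 5 | 3.0 | 0.040 |
| 10 | 20 vs 10 | 2.0 | 0.096 |
| 20 | 30 vs 20 | 1.5 | 0.20 |
| 30 | 40 vs 30 | 1.33 | 0.27 |

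This shows the mechanism only. Group C closed at 124 participants, where 124 × 0.01 = 1.24 cases would be expected. One case in 124 against none in 1000 gives Fisher p = 124/1124 = 0.11.

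**4. The continuing comparison.** New participants enter only Group A and Group B, without randomization. The protocol gives no infection rate by arm for these groups, so no between-arm distortion can be calculated from it.

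**The case against.** The strongest reply is that each case carries the label lack of efficacy. The CRF records event type (7.9.1) and 11.3.5 tabulates by type, so a reader could subtract the cases. That stands as far as it goes: separation is possible, but no sentence requires it, and the endpoint wording counts SAEs without exception.

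Second, 7.3 is not a closed list. It admits events significant for other reasons and itself makes TTS/VITT serious by rule, so 7.2 may be a deliberate designation for reporting to the authority. This also stands, and notifying vaccine failures is no error. But a designation made for notification need not decide what is counted in an incidence endpoint, and it does not supply relatedness.

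Third, table layout belongs in an SAP, which is not at hand. An SAP could indeed separate the tables. The coding rule, however, is in the protocol, and so is its tension with 7.3, 7.4 and 7.8.

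A reader might go further and infer that the SAE table will show a false safety difference between arms, or that rare serious reactions will be hidden. The documents do not support either. A difference needs unequal infection rates and pooled counting, and the protocol establishes neither. AESIs are their own component of endpoints 3 and 5 and are listed by name, and TTS/VITT is named separately; positive tests do not enter those counts. Nor does every positive test qualify: two consecutive positives within a week are needed. The safety analysis is descriptive, so the risk is misreading a total, with no false test result involved.

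**Conclusion.** The concern holds in this limited form. As written, symptom-independent infections are counted both as efficacy events and as related serious safety events, which inflates the SAE and related-SAE totals in every arm. At about 10 infections per 1000, they would be 83% to 50% of counted SAEs for other SAEs at 2 to 10 per 1000, falling to 25% at 30 per 1000.

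These shares rest on three assumptions: the SAE rate, which the protocol does not give; pooling of the labelled cases into the total; and a planning rate that covers B.1.351 only and that 11.1 itself qualifies by noting falling infection rates. Vaccine failure in 7.2 covers any variant, so the actual count could be lower or higher.

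An arm difference produced by infections alone is possible in the non-randomized A versus B comparison, where exposure may differ for reasons unrelated to the vaccines. It is not shown. The 10 versus 0 scenario is illustrative only. The change is worth making because the totals would otherwise be hard to interpret and the remedy is small.

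**What to change.** - Leave the notification of lack-of-efficacy cases in 7.2 unchanged.
- Reconcile 7.2 with 7.3, 7.4 and 7.8, so that a designation made for notification is distinct from the assessment of seriousness and causality.
- State in 7.2 and 11.3.5 that lack-of-efficacy cases are tabulated in their own category, by arm.
- State that SAE and related-SAE incidence for endpoints 3 and 5 excludes these cases unless the case itself meets the general seriousness definition in 7.3, with relatedness assessed as in 7.8.

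The cost is a wording change, one CRF flag and one extra table. What goes to the authority does not change.

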## **7.3 Serious Adverse Events**

If a serious adverse event (SAE) occurs, the investigator must alert the sponsor without unjustified delay to any AE (whether causally or not) from this study that results in one of the following outcomes, or is significant for any other reason:

- death (excluding death from progressive disease)
- a life-threatening experience – refers to an event in which the subject was at risk of death at the time of the event; it does not refer to an event which hypothetically might have caused death if it were more severe
- initial hospitalization, or prolongation of existing inpatients’ hospitalization
- persistent or significant disability or incapacity
- congenital anomaly or birth defect

Additionally all Thrombosis with Thrombocytopenia Syndrome (TTS)/Vaccine-induced Thrombotic Thrombocytopenia (VITT) will be classified as serious adverse event.

Medical judgment should be exercised in deciding whether an AE/adverse drug reaction (ADR) is serious in other situations. Important AE/ADRs that are not immediately life-threatening or do not result in death or hospitalization but may jeopardize the subject or

may require intervention to prevent one of the other outcomes listed in the definition above, should also be considered serious.

Patients should be closely observed for adverse events while receiving treatment with the IMP. Further on for 12 weeks after discontinuation from study therapy in order to detect delayed toxicity. After this period, the clinical trial medical safety desk will only be alerted to serious adverse events if the investigator believes that the event may have been caused by the investigational device or by a protocol procedure.

Events not considered to be serious adverse events are hospitalizations for the:

- routine treatment or monitoring of the studied indication, not associated with any deterioration in condition
- treatment, which was elective or pre-planned, for a pre-existing condition that did not worsen
- treatment on emergency, outpatient basis for an event not fulfilling any of the definitions of serious given above and not resulting in hospital admission.

Disease progression will not be reported as AE or SAE unless the progression is unexpected in severity or early occurrence. Progressive disease will be appropriately documented on the case report form as part of the efficacy parameters.

The study will specifically pay attention to known potential serious adverse events of special interest (AESI) describe for COVID-19 vaccines, which are non-hemorrhagic stroke, hemorrhagic stroke, acute myocardial infarction, deep vein thrombosis, pulmonary embolism, anaphylaxis, Bell's palsy, myocarditis/pericarditis, narcolepsy, appendicitis, immune thrombocytopenia, disseminated intravascular coagulation, encephalomyelitis (including acute disseminated encephalomyelitis), Guillain-Barre syndrome, and transverse myelitis.

## 7.4 Adverse Drug Reaction (ADR) & Unexpected Adverse Drug Reaction

Noxious and unintended responses to a IMP related to any dose should be considered adverse drug reactions. The phrase responses to a medicinal product means that a causal relationship between a medicinal product and an adverse event is at least a reasonable possibility, i.e. the relationship cannot be ruled out.

Regarding marketed medicinal products: a response to a drug which is noxious and unintended and which occurs at doses normally used in man for prophylaxis, diagnosis, or therapy of diseases or for modification of physiological function (see the ICH Guideline for Clinical Safety Data Management: Definitions and Standards for Expedited Reporting).

## 7.5 Suspected Unexpected Serious Adverse Reaction (SUSAR)

SUSARs are serious adverse reactions with a suspected causal relationship to the study drug that is unexpected (not previously described the SmPC or IB) and serious.

## 7.6 Pregnancy

Any pregnancy that occurs during study participation must be reported to the investigator/sponsor immediately. If a pregnancy should be confirmed after informed consent has been obtained but prior to the initiation of the study drug, the patient must be excluded from the trial.

The pregnancy must be followed up to determine outcome (including premature termination) and status of mother and child. Pregnancy complications (including spontaneous abortions) and elective terminations must be reported as an AE or SAE.

Any SAE occurring in association with a pregnancy brought to the investigator's attention after the subject has completed the study and considered by the investigator as possibly related to the IMP, must be immediately reported to the sponsor.

As the consent for the study does not cover the consent for the follow-up of the pregnancy, a separate consent has to be obtained.

## 7.7 Grading of Severity of Adverse Events

Intensity of all adverse events will be graded according to the NCI common terminology criteria for adverse events (CTCAE), version 6.0 on a five-point scale (grade 1 to 5) and reported in detail in the CRF.

Adverse events not listed in the CTCAE version xxx should be graded as follows:

| CTC grade | Equivalent to               | Definition                                                                                                                                                                                                                                           |
|-----------|-----------------------------|------------------------------------------------------------------------------------------------------------------------------------------------------------------------------------------------------------------------------------------------------|
| Grade 1   | mild                        | Discomfort noticed but no disruption of normal daily activity                                                                                                                                                                                        |
| Grade 2   | moderate                    | Discomfort sufficient to reduce or affect daily activity; no treatment or medical intervention is indicated although this could improve the overall wellbeing or symptoms of the patient.                                                            |
| Grade 3   | severe                      | Inability to work or perform normal daily activity; treatment or medical intervention is indicated in order to improve the overall wellbeing or symptoms; delaying the onset of treatment is not putting the survival of the patient at direct risk. |
| Grade 4   | life-threatening /disabling | An immediate threat to life or leading to a permanent mental or physical condition that prevents work or performing normal daily activities; treatment or medical intervention is required in order to maintain survival.                            |
| Grade 5   | death                       | AE resulting in death                                                                                                                                                                                                                                |

Mild, moderate as well as severe adverse events do not need to be serious events. Those definitions are commonly used for describing the intensity of a concrete event (e.g.: mild, moderate and severe myocardial infarction). A serious adverse event with a relatively small medical importance (e.g.: strong headache) does not necessarily need to be a severe event. For example: Nausea for several hours can be indicated as a severe adverse event, without being clinically significant. Fever with 39°C won't be graded as severe event; however, if the fever delays the discharge from hospital, it can be graded as serious adverse event. The severity of an adverse event serves as a guideline for the regulatory reporting obligation.

